## Abstract

**Background:**

Despite the health benefits of increasing physical activity in the secondary prevention of acute coronary syndrome (ACS), up to 60% of ACS patients are insufficiently active. Evidence supporting the effect of Web-based interventions on increasing physical activity outcomes in ACS patients is growing. However, randomized controlled trials (RCTs) using Web-based technologies that measured objective physical activity outcomes are sparse.

**Objective:**

Our aim is to evaluate in insufficiently active ACS patients, the effect of a fully automated, Web-based tailored nursing intervention (TAVIE en m@rche) on increasing steps per day.

**Methods:**

A parallel two-group multicenter RCT (target N=148) is being conducted in four major teaching hospitals in Montréal, Canada. An experimental group receiving the 4-week TAVIE en m@rche intervention plus a brief “booster” at 8 weeks, is compared with the control group receiving hyperlinks to publicly available websites. TAVIE en m@rche is based on the Strengths-Based Nursing Care orientation to nursing practice and the Self-Determination Theory of human motivation. The intervention is centered on videos of a nurse who delivers the content tailored to baseline levels of self-reported autonomous motivation, perceived competence, and walking behavior. Participants are recruited in hospital and are eligible if they report access to a computer and report less than recommended physical activity levels 6 months before hospitalization. Most outcome data are collected online at baseline, and 5 and 12 weeks postrandomization. The primary outcome is change in accelerometer-measured steps per day between randomization and 12 weeks. The secondary outcomes include change in steps per day between randomization and 5 weeks, and change in self-reported energy expenditure for walking and moderate to vigorous physical activity between randomization, and 5 and 12 weeks. Theoretical outcomes are the mediating role of self-reported perceived autonomy support, autonomous and controlled motivations, perceived competence, and barrier self-efficacy on steps per day. Clinical outcomes are quality of life, smoking, medication adherence, secondary prevention program attendance, health care utilization, and angina frequency. The potential moderating role of sex will also be explored. Analysis of covariance models will be used with covariates such as sex, age, fatigue, and depression symptoms. Allocation sequence is concealed, and blinding will be implemented during data analysis.

**Results:**

Recruitment started March 30, 2016. Data analysis is planned for November 2017.

**Conclusions:**

Finding alternative interventions aimed at increasing the adoption of health behavior changes such as physical activity in the secondary prevention of ACS is clearly needed. Our RCT is expected to help support the potential efficacy of a fully automated, Web-based tailored nursing intervention on the objective outcome of steps per day in an ACS population. If this RCT is successful, and after its implementation as part of usual care, TAVIE en m@rche could help improve the health of ACS patients at large.

**Trial Registration:**

ClinicalTrials.gov NCT02617641; https://clinicaltrials.gov/ct2/show/NCT02617641 (Archived by WebCite at http://www.webcitation.org/6pNNGndRa)

## Introduction

Acute coronary syndromes (ACS) are among the leading causes of coronary artery disease mortality and are among the top reasons for health care utilization in North America [1-3] and worldwide [4]. Physical activity is one behavior associated with several health benefits in ACS patients, including reduced mortality and health care utilization. Accumulating an equivalent of 150 minutes per week of moderate intensity physical activity is associated with reduced all-cause [5-7] and cardiac mortality risk [7] compared with lower levels of physical activity. Evidence from cohort data suggests that all-cause mortality risk can be reduced by accumulating half of the recommendation compared with zero minutes, and further reductions are obtained as physical activity increases [8], which may also be applicable to ACS populations. Other health benefits of increased physical activity in ACS include improved quality of life [9], reduced cardiac risk factors such as dyslipidemia and hypertension, and reduced health care utilization such as hospitalizations [10]. Moreover, positive change in one health behavior, such as an increase in physical activity, may increase overall confidence and serve as a gateway to changing other health behaviors [11], such as increased smoking cessation, healthy diet, medication adherence, or attendance in a cardiac secondary prevention program. Therefore, these multiple health benefits place increased physical activity as a cornerstone in the secondary prevention of ACS [10]. Despite these benefits, between 40% and 60% of patients were insufficiently active after an ACS event [5,6,12].

Increased physical activity is promoted in traditional secondary prevention programs that consist of face-to-face or phone health behavior change counseling, which may range from brief to intensive counseling, and most include supervised exercise in affiliated hospital settings [13]. However, only 22%-30% of cardiac patients attend face-to-face secondary prevention programs [14,15]. Barriers include the difficulty of accessing these programs among those living in remote locations where secondary prevention programs are not offered, traveling to meetings, or reaching those who lack motivation or are unwilling to participate in these programs. Therefore, alternative ways of delivering these programs are being examined in research, including use of the Web [13].

Web-based interventions aimed at improving health behaviors have been tested mostly in general adult populations. These interventions include modes of delivery such as online text, videos, and discussion forums, and include other modes complementary to websites such as email and text message [16]. A meta-analysis of randomized controlled trials (RCTs) and quasi-experimental studies in mainly general adult populations or adults with cardiac risk factors found a significantly greater effect on physical activity outcomes in Web-based interventions compared with usual care control groups that were not Web-based (*d*=0.14, *P*<.001) [17]. Although intervention effects were small, a greater effect was found in studies that included only insufficiently active participants compared with those that included any level of physical activity (*d*=0.37 vs 0.12, respectively, *P*<.05) [17].

Web-based tailored interventions are expected to increase the relevancy of and attention to the information delivered, which in turn is expected to improve effects on health behavior change [18,19]. Tailoring can be static, such that tailored messages are provided based on a single baseline assessment, or dynamic, such that tailored messages are provided based on multiple assessments from baseline to follow-up [20]. Although a meta-analysis of RCTs and quasi-experimental studies in mainly general adult populations or adults with cardiac risk factors found no differences between tailored versus non-tailored interventions on physical activity outcomes, the authors found a significant effect in favor of tailoring (static or dynamic) on smoking cessation and healthy diet outcomes [21]. Therefore, increased physical activity in Web-based interventions may not depend only on tailoring. Perhaps the combination of components within Web-based tailored interventions matters, such as the variables on which tailoring was based (eg, motivation and confidence), modes of delivery used (eg, combining online text, videos, email, and others), level of intervention intensity delivered, and target population characteristics. Therefore, further research is needed to test innovative combinations of these components in tailored interventions to influence greater increases in physical activity.

In ACS patients, a Cochrane review found some evidence in eight RCTs to support the effect on increased physical activity outcomes in favor of Web-based interventions (tailored or not) compared with usual care [22]. However, heterogeneity between these RCTs prevented a meta-analysis on physical activity outcomes [22]. Among these eight RCTs, one was a pilot [23], two were not powered on physical activity outcomes [24,25], and one was powered on a self-reported physical activity outcome, but results were limited by the majority of participants dropping out [26]. Only four RCTs were full-sized and powered on objective physical activity outcomes [27-30], among which, two tested tailored interventions [27,28]. Both found significantly greater levels in the primary outcome of steps per day in favor of the tailored experimental groups [27,28]. These data suggest that in ACS populations, the effects of tailored interventions on steps per day outcomes are promising.

The other two RCTs tested nontailored interventions measuring the primary outcome of exercise capacity compared with usual care [29,30]. One RCT found a significantly greater increase in a proxy outcome of exercise capacity, maximal time on treadmill, in favor of the experimental group [29]. In contrast, the other RCT found no difference between groups in treadmill-measured peak oxygen uptake, despite finding significantly greater increases in a subjective secondary outcome of self-reported physical activity in favor of the experimental group [30]. Considering these four RCTs, the content of the Web-based interventions tested were sufficient to increase steps per day [27,28] and maximal time on treadmill [29], but the exercise intensity was insufficient to increase peak oxygen uptake [30]. No RCTs tested Web-based interventions, with or without tailoring, in ACS patients performing insufficient physical activity. The paucity of strong evidence highlights the need for future full-sized RCTs testing Web-based tailored interventions on objective physical activity outcomes in ACS populations.

### Theoretical Framework

We designed the fully automated, Web-based tailored nursing intervention TAVIE en m@rche in French. “TA VIE” means *your life*, and “en marche” means *walking* as the intervention is focused on increasing walking behavior in one’s daily life after an ACS-related hospitalization. The tailored content of TAVIE en m@rche is presented to participants by prerecorded videos of a nurse. We used Strengths-Based Nursing Care (SBNC) integrated with Self-Determination Theory (SDT) as the intervention’s theoretical framework. SBNC describes an orientation to nursing practice or a “way of being” that is manifested through person-centered, holistic, knowledgeable, and compassionate nursing care [31]. SBNC is driven by eight values that focus on “understanding the whole, … and understanding how strengths and weaknesses interact to promote health, and healing” (p. 120) [31]: (1) health and healing refers to creating and restoring persons’ sense of wholeness in all domains of human functioning, (2) uniqueness of the person refers to understanding unique experiences and strengths, (3) holism and embodiment refers to understanding the complexities underlying the relationships among the mind, brain, and other body systems, (4) objective/subjective reality and created meaning refers to understanding along with objective observations, subjective realities through created meanings of persons’ experiences, (5) self-determination refers to respecting persons’ right to a life grounded in volition and free will, (6) person and environment are integral refers to understanding how persons’ environments influence health and healing, (7) learning, readiness, and timing refers to being sensitive to readiness and timing when engaging patients in an active learning or change process, and (8) collaborative partnership between nurse and person refers to both nurse and patient sharing knowledge and strategies that foster health and healing.

Self-determination, one of the eight SBNC values, is particularly relevant in nursing care, and in human motivation to adopt health behavior changes. This value was drawn from literature on self-determination including past works on the SDT of human motivation [32]. Empirical work in SDT applied in health care settings has presented two models [33]. The first model suggests that improvements in physical and mental health can be explained by the satisfaction of the psychological needs of autonomy, competence, and relatedness [33]. However, our Web-based intervention that has a minimal focus on encouraging social support from others may not be powerful enough to influence the construct of relatedness, which refers to the “feeling of being respected, understood, and cared for by others” (p. 327 [33]), such as exercise companions. Therefore, the second model that excludes the construct of relatedness [33] was retained. This model suggests that improvements in health behavior can be explained by improvements in three SDT constructs: increased perceived autonomy support, improved self-determined motivation (decreased controlled vs increased autonomous motivations), and increased perceived competence [33,34]. Perceived autonomy support refers to the perception that during an intervention or interaction with a significant other, choices were provided, rationale was offered, and acknowledgement or empathy was expressed [33]. Controlled motivation refers to actual or future behavior change that is imposed by others or that is motivated out of a sense of guilt and shame in the presence of failure in change [33]. Autonomous motivation refers to actual or future behavior change that is volitional, aligned with one’s goals and values, or motivated by sheer enjoyment [33]. Perceived competence, similar to self-efficacy [34], refers to the degree of confidence in one’s capability in achieving a health behavior change goal [33]. From the cardiac literature, barrier self-efficacy refers to degree of confidence in overcoming barriers towards health behavior change [35]. A systematic review found that the relationships between these SDT constructs and physical activity outcomes were well supported [36], suggesting that interventions that are efficacious at influencing positive changes in SDT constructs may also influence improvements in physical activity outcomes.

SDT is a novel approach to theoretical grounding in the Web-based physical activity literature as no studies using SDT were found in past meta-analyses in either general adult populations [17] or ACS patients [22]. However, we found three full-sized RCTs testing the effect of Web- and SDT-based interventions in general adult populations that were powered on self-reported physical activity outcomes [37,38] or a composite outcome that included physical activity [39]. Among the two RCTs powered on a self-reported physical activity outcome, the most recent found a significant increase of 71 minutes in weekly moderate to vigorous physical activity at 12 months in favor of the SDT-based intervention compared with a waitlist control [37]. In this RCT, the SDT-based intervention consisted of tailored messages delivered in text format and nontailored information (motivational and educational) delivered by videos of a physical activity expert. In the other RCT, the authors did not report effects on physical activity outcomes in their conference abstract [38]. In the RCT powered on a composite outcome of self-reported weight, diet, smoking, and physical activity, the authors reported no effect on the physical activity outcome, which was possibly due to a lack of intervention utilization because too many choices were given in intervention intensities and modes of delivery in the experimental group [39]. Therefore, the Web- and SDT-based intervention literature is sparse [37-39], despite the solid evidence supporting the positive associations between SDT constructs and physical activity outcomes [36]. To our knowledge, no RCT has tested a Web- and SDT-based intervention on physical activity outcomes in ACS patients whether sufficiently active or not. In addition, an innovation not yet examined in the Web-based ACS literature is the use of fully automated videos in tailored interventions. Use of videos could better convey the nurses’ strengths-based “way of being” because patients can view and listen to the nurse who presents tailored motivational and educational information instead of reading this same information in text format.

### Study Aim and Hypotheses

The aim of this RCT is to evaluate in insufficiently active ACS patients, the effect of a fully automated, Web-based tailored nursing intervention (TAVIE en m@rche) on increased steps per day. Our primary hypothesis is that ACS patients in the experimental group receiving TAVIE en m@rche compared with the control group receiving hyperlinks to publicly available websites will demonstrate a greater increase in change in steps per day between randomization and 12 weeks (H1). Secondary hypotheses are a greater increase in change in steps per day between randomization and 5 weeks (H2), and in energy expenditure for walking and moderate to vigorous physical activity between randomization and 5 weeks, and randomization and 12 weeks (H3 to H6).

We are interested in assessing if the change in SDT variables immediately postintervention at 5 weeks will explain the hypothesized increase in steps per day at 12 weeks. Therefore, we will explore the mediating role of the SDT constructs (perceived autonomy support, controlled and autonomous motivations, perceived competence) and barrier self-efficacy on the effect of TAVIE en m@rche on increased steps per day at 12 weeks (H7 to H11 respectively).

We will also explore the effect of TAVIE en m@rche at 12 weeks on improved quality of life (global, emotional, physical, and social), smoking, medication adherence, secondary prevention program attendance, emergency visits, and hospitalizations (H12 to H20). The potential moderating role of sex on the effect of TAVIE en m@rche on steps per day at 12 weeks will also be explored (H21). Finally, we expect no adverse effect, which is represented by an equal level of angina symptom frequency at 12 weeks in both groups (H22).

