### Sample Size Calculation

To detect a difference in change between randomization and 12 weeks of 1500 steps per day (SD 2824) in favor of the experimental group compared with the control group, a total of 148 participants (n=74 participants per group [57 plus 17 for attrition], and n=37 per recruitment center) is needed, given a two-sided 5% significance level, power of 80%, and an expected attrition of 23%. The 1500 steps per day is an approximation of half of the recommended daily minutes of moderate intensity physical activity [47]. The attrition of 23% was reported in a meta-analysis of Web-based interventions, in which the experimental groups had an average intervention duration of 13 weeks [17]. The SD of 2824 steps per day was estimated using data found in an RCT of a counseling intervention in ACS patients in Quebec [48].

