Data for both emergency department visits and hospitalizations are collected from the medical records at 12 weeks at each study center. For each outcome, one or more emergency department visits or hospitalizations for any reason indicate a score of 1 and no emergency department visits or hospitalizations indicate a score of 0.

Angina frequency is assessed at baseline and 12 weeks by the angina frequency scale of the Seattle Angina Questionnaire. This measure assesses frequency of angina pain and nitroglycerin use that we changed from “in the past 4 weeks” to “in the past 2 weeks.” The score is the sum of responses of 2 items rated between “4 or more times per day” (1) and “none over the past 2 weeks” (6), which is then transformed to score between 0 (worst) and 100 (best). Lower scores represent greater angina frequency. A reported significant positive association was *r*=.31 between greater angina frequency and greater number of refills of sublingual nitroglycerin tablets in the previous year [62].

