### Ethical Considerations

Ethics approval for this multicenter RCT was obtained from the Scientific and Ethics Committee of the Montreal Heart Institute Research Center (reference #MP-33-2015-1887). Procedures follow the mechanism of multicenter studies outlined by the Quebec Ministry of Health and Social Services [67].

We expect that the study population has no additional adverse effects in participating in this RCT because the recommendation for physical activity (ie, walking 150 minutes per week) is consistent with current cardiology practice. Also, past research found that cardiac patients can safely participate in physical activity at home [68,69]. As such, we hypothesize that angina frequency will be equivalent in both groups (experimental vs control).

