#### Outcomes

First, although our primary outcome of steps per day was retained based on the literature showing the association between increased physical activity and reduced mortality in ACS patients [5-7], we did not plan mortality as primary or secondary outcomes. Trials that aim to improve physical activity outcomes usually establish eligibility criteria to select populations that are capable of attaining the amount of physical activity recommended in the intervention. As such, these populations have few comorbidities resulting in low serious adverse cardiac events or mortality. Two RCTs testing Web-based interventions in ACS patients measured an objective physical activity outcome (steps per day or exercise capacity) and reported serious adverse cardiac or mortality events requiring hospitalization per treatment group [28,29]. Reid et al. reported four hospitalisations for chest pain and no deaths in the experimental group, and six hospitalisations for chest pain, one for cardiac surgery and two deaths in the control group during 12 months of follow-up [28] Lear et al. reported three (9%) major cardiac events (e.g., revascularisation, stroke, and death) in the experimental group, and six (16%) in the control group during 16 months of follow-up [29]. These data suggest that fewer serious adverse cardiac or mortality events are found in favor of Web-based experimental groups, and too few events occur to plan mortality as a primary or secondary outcome within a feasible timeframe.

Second, for our secondary outcome of energy expenditure, we plan estimates from self-reported data instead of from accelerometer data. Accelerometers require the entry of participants’ weight in the devices to produce the estimates. However, we do not collect data on weight from participants at home before randomization (baseline [-T1]) because these data may be missing or unreliable from self-report or from participants’ own weighing scales.

Third, we planned a relatively short follow-up of 12 weeks for feasibility reasons as this RCT is part of a doctoral degree. A longer follow-up on steps per day and other health behavior changes in a future RCT testing TAVIE en m@rche could improve clinical relevance.

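### H22 equates the absence of adverse effects with equal 12-week angina scores, leaving out deaths and the emergency visits and hospitalizations that the trial already collects

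*Protocol article*

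**What the plan says.** **Safety hypothesis.** Study Aim and Hypotheses closes with: "Finally, we expect no adverse effect, which is represented by an equal level of angina symptom frequency at 12 weeks in both groups (H22". Ethical Considerations repeats it, again with angina only: "As such, we hypothesize that angina frequency will be equivalent in both groups (experimental vs control".

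**Instrument.** Under Clinical Outcomes: "Angina frequency is assessed at baseline and 12 weeks by the angina frequency scale of the Seattle Angina Questionnaire". The authors shortened its recall period, "that we changed from “in the past 4 weeks” to “in the past 2 weeks". Table 2 places angina among the questionnaires completed at home. Timeline and Procedures says that the follow-up questionnaires are completed online, after a week of accelerometer wear.

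**Record-based events.** Emergency visits and hospitalizations are collected at 12 weeks from medical records at each study center and reduced to two binary outcomes: "one or more emergency department visits or hospitalizations for any reason indicate a score of 1". Study Aim and Hypotheses lists them within H12 to H20, the outcomes that the intervention is expected to improve. Under Statistical Methods, dichotomous outcomes without a baseline value are compared by chi-square, and proportions per group are to be given with 95% confidence intervals.

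**Deaths.** The Limitations text on outcomes says that mortality was not planned as a primary or secondary outcome because too few events are expected. Neither the Outcomes section nor Table 2 lists deaths.

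**The concern.** The article sets an operational rule for when the intervention may be called free of adverse effects, and the rule has one component. It cannot register a death. It also need not register a cardiac readmission: a participant admitted in week 3 who has no angina in the two weeks before the form gets the best possible score. A participant who leaves the study after an event has no observed score.

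The data that would register an admission are in the trial, but under hypotheses about benefit and with no link to H22. Participants are recent ACS patients who are encouraged to walk more from the fourth or fifth week after discharge. A statement that no adverse effect was found is one that readers will rely on, and as defined it could be made without looking at admissions or deaths.

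**Working it through.** The point concerns a definition, so the main check sets the rule against the events it should cover. The arithmetic gives the scale.

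**1. What H22 registers**

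| Event between randomization and 12 weeks | Counts against H22? | Seen elsewhere in the plan? |
|---|---|---|
| Angina in the two weeks before the 12-week form, form returned | Yes | – |
| Angina earlier, resolved by then | No | Only if it led to an emergency visit or admission |
| Cardiac admission, then symptom-free, form returned | No | Yes, as any-cause hospitalization without its cause |
| Cardiac admission, form not returned | No observed score | Yes, if it is in a study center's records |
| Death | No observed score | No listed outcome |

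The recall period covers 2 of 12 weeks: 2/12 = 17% of the follow-up.

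**2. The plan's own figures.** These are 1500 steps per day, SD 2824, two-sided 5%, 80% power and 23% attrition (Sample Size Calculation). The normal approximation gives 2 × (2824/1500)² × (1.960 + 0.842)² = 55.6, so 56 per group. The two-sample t test needs 57 (power 80.3%). Then 57/(1 − 0.23) = 74.03, stated as 74 per group and 148 in total. The figures reproduce. H22 has no sample size of its own.

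**3. Expected number of events.** The Limitations text cites one trial with major cardiac events in 9% (experimental) and 16% (control) over 16 months. Assuming a constant rate, with 16 months = 69.6 weeks:

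- 1 − (1 − 0.09)^(12/69.6) = 1.6%; × 74 = 1.2 events
- 1 − (1 − 0.16)^(12/69.6) = 3.0%; × 74 = 2.2 events

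This gives about 1 to 2 per arm. The rate soon after ACS may be higher; the article gives no figure for it.

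**4. What an angina mean shows of such events.** For illustration, assume that every scored participant in both arms averages 90 of 100. If k of 74 experimental participants die or leave after an event and have no score, the difference among those scored is 0. Scoring them 0 (worst) would lower the experimental mean by 90k/74: 2.4 points for k = 2 and 4.9 points for k = 4. The values 90 and 0 are assumptions. The example shows the mechanism and is not a forecast.

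**5. What counts with exact intervals would show.** Two-sided Clopper-Pearson limits with 74 randomized per arm:

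- 0/74: 0 to 4.9% (upper limit 1 − 0.025^(1/74))
- 1/74 = 1.4%: 0.03% to 7.3%
- 2/74 = 2.7%: 0.3% to 9.4%

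A test would add little. Even 9% against 16%, the full 16-month rates, has about 25% power at 74 per group, and 80% power needs about 350 per group.

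**The case against.** The strongest reply is that the trial is not blind to harm. Emergency visits and hospitalizations come from records in both arms and do not depend on the questionnaire. A chi-square test has no direction, and group proportions with confidence intervals are promised. Listing these outcomes as expected improvements does not hide an excess in the experimental arm. This stands, and it limits the point to what H22 may be taken to conclude.

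The text also gives a reason for not making mortality an outcome: too few events. That is sound as a reason not to power on mortality. It is no reason to leave deaths out of a statement about adverse effects.

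A condensed article may leave serious-event recording and chart-form fields to the full protocol. That stands too, so the absence of such detail is not the finding. The finding is the definition that the article states twice.

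Three stronger readings are tempting and not supported:

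- A reader might infer that the 17 of 74 per arm allowed for attrition are the harmed participants. The 23% is a planning figure from a meta-analysis of Web-based interventions. With 1 to 2 cardiac events expected per arm, most of those 17 would be ordinary dropouts, and a readmitted survivor can still return the form.
- A reader might infer that these few events would decide the safety question. One against two events decides nothing, as the intervals above show.
- A reader might wish to fault the Discussion sentence "These data suggest that fewer serious adverse cardiac or mortality events are found in favor of Web-based experimental groups". It is hedged, it rests on two trials that point the same way, and it fixes no analysis.

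**Conclusion.** The point holds in a limited form. As written, H22 can be declared met on a two-week self-report among those who answer, whatever the deaths and admissions by arm. Admissions would still appear in their own any-cause comparison, without their cause and unconnected to the safety statement. Deaths have no listed place.

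The size is modest: about 1 to 2 major cardiac events per 74 in 12 weeks, assuming that the cited 9% and 16% apply here and accrue evenly. The primary outcome, the sample size and the main analysis are unaffected. What changes is the conclusion that the trial may draw about adverse effects. The missing-data method is left open, so imputation of angina scores is possible, but the article states no rule by which a death or cardiac event would count as a bad result.

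**What to change.** 1. In Study Aim and Hypotheses and in Ethical Considerations, limit H22 to no difference in angina frequency at 12 weeks, and do not infer the absence of adverse effects from it alone.
2. Base any statement on adverse effects on angina frequency together with deaths and emergency visits or hospitalizations from randomization to 12 weeks. Show these events for any cause, and separately for cardiac cause as recorded in the chart.
3. Use all randomized participants as the denominator, and report counts by arm with exact 95% intervals, without a significance test.
4. At the 12-week chart review already planned, record the date and cause of each event and vital status. Cause should be classified by someone unaware of the assigned group: the Blinding section says that the first author knows the assignment, and the anonymization described there covers only the data completed online.

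**Cost.** A few more fields in an existing chart review, a blinded classification step and some rewording. Counts will be small and cannot support a powered comparison. Study-center records may miss events treated elsewhere, and the report should say so.
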